## Abstract

**Background:**

Despite its well-known benefits for health and well-being physical activity levels are insufficient and declining with age in Germany. Physical activity promotion programs for older adults are often not successful, one reason is insufficient relevance of intervention measures for the study population. Community-based participatory research (CBPR) is a possible key strategy for tailoring more meaningful intervention programs to a specific community. However, evidence for the effectiveness of CBPR in the general population is scarce. This study aims to formally evaluate the efficacy of a CBPR approach for developing and implementing an outdoor physical activity program for older adults.

**Methods/design:**

The OUTDOOR ACTIVE intervention trial is a cluster-randomised intervention study carried out in a random sample of eight subdistricts in the city of Bremen, Germany. The eight subdistricts are grouped into four homogenous pairs with regard to socioeconomic level and land use mix of the subdistrict. Within the pairs, the subdistricts are assigned randomly to the two study arms: participatory development and implementation of a community-based program to promote outdoor physical activity (intervention) versus no intervention (controls). For evaluation, a survey is carried out before (baseline) and after (follow-up) the intervention period. The measurements include 7-day accelerometer measurement, physical fitness test, blood pressure, basic anthropometry, and self-administered questionnaire.

**Discussion:**

The OUTDOOR ACTIVE intervention trial will provide detailed information on PA intervention for older adults in an urban setting. Through the participatory nature of the study it will provide valuable insights into drivers and barriers to PA in this group, and it will inform policy makers and other stakeholders how to benefit from the results.

**Trial registration:**

German Clinical Trials Register DRKS00015117 (Date of registration 17-07-2018).

## Background

The current demographic change in Europe is characterized by decreasing birth rates, rising life expectancy and an ageing population. This development is posing challenges on private, social and societal levels, and healthy ageing has become one key strategy to fight the expected added burden of the health system [1]. Physical activity (PA) is declining with age, and it is less prevalent in women compared to men and in lower compared to higher socioeconomic groups [2]. Despite its known benefits for health, more than two-thirds of the age group 65 years and older do not meet minimal PA recommendations in Germany [3] and raising these levels, preferably in community-based or neighborhood-based settings, forms one of the seven national specific health targets in the area of healthy ageing [4]. Cochrane reviews on PA promotion have repeatedly criticized the lack of intervention studies with sound methodology using objective PA measurements for evaluation [5–7].

Various factors of all ecological levels (intrapersonal, interpersonal, and environmental) contribute to the uptake and maintenance of any type of PA [8]. However, due to a lack of longitudinal studies and studies using objective PA measurements, a differentiation between correlates and determinants is barely possible [7, 8]. Factors that could play a causal role for PA in adults in general are perceived fitness, intention to exercise, self-efficacy, social support, PA history, and other psychosocial variables [8–11]. Apart from these intra- and interpersonal characteristics, the engagement in PA is strongly dependent on environmental factors [8, 12–14] and environmental intervention has been shown to be potentially successful previously [15]. Research in older adults is still scarce; a review from 2004 implies that among environmental factors, safety and aesthetics could play the most important roles in older age groups [16]. A review by van Cauwenberg and colleagues on determinants for PA [17] found inconsistent results for the age group 65+, which the authors attribute to “methodological issues within this developing research field”. Only two of the 29 included studies were using objective PA measurements, and most studies failed to differentiate between types of activity. The latter would be important for detecting associations between PA and environmental factors [17]. As any engagement in PA, outdoor PA has direct beneficial health effects on muscle strength, motor skills and cardiorespiratory fitness. Outdoor PA also has indirect effects that are not attributed to the physical movement alone, including higher Vitamin D levels, mental wellbeing and raised emotional scores through exposure to sensory engagement [18]. EEC readings show the direct impact of the PA environment [19]. In a recent study, older adults who were physically active outdoors at least once a week showed higher levels of PA compared with those who were physically active indoors only [20]. Moreover, outdoor PA gives the opportunity for social interaction and does not require sports facilities.

The success of PA promotion programs is heterogeneous [21, 22] and depends amongst others on the type of intervention and presence of a methodological framework for the development of the intervention [23]. Community-based participatory research (CBPR) frameworks show great potential for PA intervention as they involve the community, especially if they follow an ecological model [10]. CBPR have been shown to be effective for work-related health promotion [24], and they are useful to reduce health disparities [25]. Experience with CBPR in the development of PA promotion programs in older adults is limited. Despite the poor evidence base, PA interventions following a social ecological approach and integrating individual and environmental levels are considered to be most effective [8–11].

The OUTDOOR ACTIVE study is part of the *Physical Activity And Health Equity: Primary Prevention For Healthy Ageing (AEQUIPA)* project, a regional prevention research network in Northwest Germany funded by the German Federal Ministry of Education and Research (BMBF). The AEQUIPA research network includes several interlinked projects which employ theory-based empirical research methods to develop, implement and evaluate PA and mobility interventions for older adults aged 65–75 years. The network’s overall aim is to strengthen the evidence base for PA in the context of healthy ageing [26]. AEQUIPA is in its second funding phase (02/2018–01/2021), the first funding phase started in 02/2015. In the OUTDOOR ACTIVE pilot study, which took place during the first funding phase, a community-based physical activity program was developed in one urban district in the city of Bremen, Germany, where a CBPR approach, the PRECEDE-PROCEED model (PPM), was used [27]. Based on the experiences, a short track PPM for participatory development of PA programs in older adults in urban settings was developed. Moreover, an open toolbox of ready-to-use intervention components to be used in the participatory process was started and will be continuously updated.

The objective of the OUTDOOR ACTIVE intervention trial is to formally test and investigate efficacy of the developed short track PPM. For this, a cluster randomized trial (CRT) will be carried out in eight random subdistricts in the city of Bremen, Germany. In four of the randomly selected subdistricts, the short track PPM will be applied and the resulting intervention program implemented, the other four randomly selected subdistricts will serve as controls, where no intervention is taking place.

## Methods/design

### Study setting and participants

The OUTDOOR ACTIVE intervention trial will be taking place in randomly selected subdistricts of the city of Bremen. The city municipality of Bremen is located in north western Germany with around 560,000 inhabitants. Bremen is organised hierarchically into 5 boroughs, 23 urban districts and 88 subdistricts. The first randomization unit are the subdistricts, where less populated subdistricts (with less than 500 inhabitants aged 65–75 years) and the five subdistricts of the OUTDOOR ACTIVE pilot study are excluded, leaving 53 subdistricts eligible for the study (see Fig. 1). The subdistricts of the city of Bremen are highly heterogeneous e.g. with respect to SES indicators (e.g. proportion of residents with low school education ranging from 18.5 to 89.2%, medium taxable income ranging from 10,069 € to 35,995 €), life expectancy (ranging from 72.4 [78.2] years to 81.0 [85.3] years in males [females]) or land use mix (e.g. proportion of recreational area ranging from 0.1 to 66.9%; all data from [28]).

**Fig. 1 Fig1:**
[figure not shown]
The OUTDOOR ACTIVE intervention trial

Persons eligible for the study are non-institutionalized adults, aged 65–75 years residing in the sampled subdistricts. Depending of the number, either a simple random sample or the full sample of eligible participants will be invited to the study. Persons not able to give consent will be excluded.

### Interventions

The eight subdistricts are manually grouped into homogenous pairs with regard to community socioeconomic status and land mix use. From these pairs, one intervention subdistrict is randomly chosen, the remainder serves as control subdistrict.

A physical activity program tailored to the specific situation in the respective subdistrict will be developed in each of the intervention subdistricts with active involvement of the general public and other stakeholders. For tailoring, data from situational analysis, baseline surveys, and participatory actions (community forum, workshops, and excursions) is used. Each development step is communicated and discussed in the community and tested for its feasibility. The intervention material is being developed as part of an ecological model [16]. Implementation will be done with the help of local stakeholders and key actors of the population to ensure sustainability. A community round table with all stakeholders will take place throughout the intervention phase in the intervention subdistricts.

### Outcomes

For the formal CRT evaluation, baseline and follow up surveys are carried out in the eight study subdistricts. These include 7-days measurements of physical activity (3D accelerometer, ActiGraph, Pensacola (FL)) and fitness (modified Senior Fitness Test [29]) a short physical examination (blood pressure, short anthropometry) and a self-administered questionnaire on intrapersonal, interpersonal, and environmental determinants of physical activity. Training sessions on fitness test and physical examination are held regularly for the field staff to ensure standardised measurements.

The primary outcome is amount of PA measured by accelerometer in average counts per minutes (CPM). The secondary outcome is physical fitness. The tests are handgrip strength, chair stand, 2-min step, back scratch, sit and reach, and flamingo balance test. Further secondary outcomes are time spent outdoors in minutes per day (measured by questionnaire) and inactivity in hours per day (measured by questionnaire). The impact evaluation will include identified key determinants. Evaluation of efficacy and possible adverse effects of the PA promotion will be done stratified by sex. Mixed models will be used to account for the clustered structure of the data introduced by the two-stage sampling design.

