**Fig. 2 Fig2:**
[figure not shown]
Timeline of the OUTDOOR ACTIVE intervention trial

The sample size calculation is based on data gathered during the OUTDOOR ACTIVE pilot study. Accelerometer-based average counts per minute (CPM) will be used for evaluation. Mean CPM ranged from 1587.5 (SD 470.7) to 1697.0 (SD 440.5) in the five highly heterogeneous subdistricts (ICC = 0.0024). CPM were consistently higher in women than in men with only moderate differences for SES. In the OUTDOOR ACTIVE intervention trial, a mean difference of 150 CPM (equivalent to standardized effect size of 0.33) is targeted. Assuming a fixed number of clusters (four intervention, four control), 204 participants will be needed in each study arm (significance level 5% two-sided, power 90%) summing up to 808 for sex-stratified trial evaluation. Assuming a fixed proportion of 30% for dropouts, 144 participants (72 female, 72 male) are needed in each of the subdistricts at baseline.

Since no intervention is developed in the control subdistricts, and active involvement of the study participants is required in the intervention subdistricts, blinding was not a feasible option for the intervention trial. Instead, for communication with the public, the study is separated into two parts: one part containing the surveys (“BUTEN AKTIV Gesundheitsuntersuchung” OUTDOOR ACTIVE health surveys), which take place in all eight subdistricts and focuses on longitudinal aspects of the ageing process; the second part containing the intervention development and implementation, takes only place in the four intervention subdistricts (“BUTEN AKTIV vor Ort” OUTDOOR ACTIVE on-site). Thus, participants of the survey might or might not be aware of the intervention development.

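### The article names only a sex-stratified evaluation of adverse effects; an overall comparison of women and men together should be added (minor)

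*Protocol article*

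**What the plan says.** The Outcomes section of the protocol article puts efficacy and harm under one rule: "Evaluation of efficacy and possible adverse effects of the PA promotion will be done stratified by sex". The next sentence adds: "Mixed models will be used to account for the clustered structure of the data introduced by the two-stage sampling design". This is all the article says about how harms will be analysed. It names no adverse-effect measure and gives no expected rate.

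The section on participant timeline, blinding and sample size shows what the stratification means. The target is CPM: "a mean difference of 150 CPM (equivalent to standardized effect size of 0.33) is targeted". The calculation gives one comparison: "Assuming a fixed number of clusters (four intervention, four control), 204 participants will be needed in each study arm". It is then doubled, "summing up to 808 for sex-stratified trial evaluation", and carried to recruitment: "Assuming a fixed proportion of 30% for dropouts, 144 participants (72 female, 72 male) are needed in each of the subdistricts at baseline". The doubling makes sense only if women and men each form a two-arm comparison of their own. The same paragraph remarks that CPM was consistently higher in women than in men. It gives no sex-related reason for splitting harms.

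**The concern.** Sex stratification here is a feature of the efficacy design. It was paid for by doubling the sample for CPM and then extended to adverse effects without a reason of its own. A reader weighing the safety of an outdoor activity programme for people aged 65–75 first needs one overall arm difference with its interval. The Discussion foresees extending the programme to all subdistricts of Bremen if it succeeds, so that figure would be used.

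Under the rule as worded, the report would give two harm comparisons, each from half of the people available, and no combined one. Each interval would be wide. If both were read by significance at 5%, the chance of a false alarm in at least one sex would be near 10%. The participants who could give a tighter overall answer would already have been recruited and measured.

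**Working it through.** **Inputs from the article.** Four subdistricts per arm, ICC 0.0024, two-sided 5%, power 90%, target difference 150 CPM, pilot SDs 440.5 and 470.7, total 808, dropout 30%, 144 per subdistrict at baseline.

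**Inputs assumed.** Harm risks, because the article gives none; a binary harm; the same risk in both sexes unless stated otherwise; and the CPM ICC as a stand-in for the ICC of a harm.

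**1. The plan's own figure.**
- Individual-level size with SD 440.5: n0 = 2 × (440.5 × (1.960 + 1.282) / 150)² = 181.2 per arm.
- With k = 4 clusters per arm: n = n0 × k × (1 − ICC) / (k − n0 × ICC) = 181.2 × 4 × 0.9976 / (4 − 0.435) = 202.9. Rounded up to 51 per cluster, this is 204, as stated.
- Two small side remarks do not affect this point. The stated effect size of 0.33 would give about 218. Four times 204 is 816, not 808.
- 808 / 8 = 101 per subdistrict, and 101 / 0.7 = 144.3, stated as 144.

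The 204 is therefore a one-sex figure for CPM.

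**2. People per harm comparison.** 808 / 4 = 202 per arm in one sex. 808 / 2 = 404 per arm with both sexes.

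**3. Precision.** Half-width = 1.96 × √(2 × p(1 − p) × DE / n), with p = 0.10 in both arms and DE = 1 + (m − 1) × 0.0024.
- One sex: m = 50.5, DE = 1.119, half-width = 1.96 × √(0.18 × 1.119 / 202) = 0.062.
- Both sexes: m = 101, DE = 1.240, half-width = 1.96 × √(0.18 × 1.240 / 404) = 0.046.

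The combined interval is about a quarter narrower (4.6 / 6.2 = 0.74). The gain is less than doubling n would suggest, because the design effect grows with the number per subdistrict.

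**4. Detection, no clustering.** Power = Φ((d − z × SE0) / SE1), with SE0 from the mean risk and SE1 from the two separate risks. For 10% against 15%:
- One sex at 5%: (0.05 − 1.960 × 0.0329) / 0.0328 = −0.44, power 33%.
- Flag in at least one sex, each tested at 5%: 1 − (1 − 0.33)² = 55%. The false-alarm rate is 1 − 0.95² = 9.75%.
- Both sexes together at 5%: (0.05 − 1.960 × 0.0233) / 0.0232 = 0.19, power about 58%.
- Two sex-specific tests with the overall false-alarm rate held at 5%: each at 1 − √0.95 = 2.53%, z = 2.24. Then (0.05 − 2.24 × 0.0329) / 0.0328 = −0.72, power 24% in each sex, and 1 − (1 − 0.24)² = 42%.

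| Assumed risks | One sex | Either sex, each at 5% | Both sexes together |
|---|---|---|---|
| 10% v 15%, no ICC | 33% | 55% | 58% |
| 10% v 15%, ICC 0.0024 | 30% | 50% | 49% |
| 5% v 10%, no ICC | 48% | 73% | 77% |
| 5% v 10%, ICC 0.0024 | 44% | 67% | 68% |

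The either-sex figures with the ICC allow for the correlation that arises because both sexes share the same subdistricts.

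**5. Harm in one sex only.** If 5% against 10% holds in one sex and there is no excess in the other, the combined contrast is 5% against 7.5%. Power is then 31% combined and 48% within the affected sex (26% and 44% with the ICC).

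**The case against.** The strongest reply is that looking by sex does not hide harms. A reader might compare the 33% within one sex with the 58% for the sexes together and infer that a real harm is easy to miss. The rule looks at both sexes, however, and a signal is missed only if both comparisons miss it. The table shows that the chance of at least one flag is then close to the combined power, and with the ICC the gap all but vanishes. This stands. What remains is that the near-equality is bought with about twice the false-alarm rate, and that it does nothing for the width of the intervals.

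Three further replies also have weight:

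- **The sample was doubled.** Each sex has about the number planned for the primary outcome. The halving is relative to the combined 808, not a shortfall against the design. But that number was chosen for 150 CPM and says nothing about harms.
- **By-sex results have value of their own.** Step 5 shows that a harm confined to one sex is seen better by sex. Reducing those results to a descriptive breakdown would carry a cost.
- **This is a condensed article.** It does not exclude a combined harm table, and the full protocol or analysis plan may contain one. A reader might infer that no combined estimate will be reported; the text does not say so. It does state a specific rule for harms, though, and that rule names only the by-sex evaluation.

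The harm figures are also hypothetical. Several listed measures are continuous. For such a measure the standardized difference detectable with 90% power is about 0.34 in one sex and 0.25 combined (ICC 0.0024).

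**Conclusion.** The point holds as a minor one. The article's only rule for adverse effects is a sex-stratified evaluation, which it sizes and explains for CPM alone. Applied as worded, it yields two comparisons of about 202 per arm and leaves the overall estimate from about 404 per arm unused. At an assumed 10% risk the cost is a half-width of 6.2 rather than 4.6 percentage points. At a matched 5% false-alarm rate, the chance of detecting 10% against 15% is about 42% rather than 58%.

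These sizes rest on assumed risks, a binary harm, equal harm in both sexes and, for the half-widths, an ICC borrowed from CPM. Large harms would be seen fairly well either way (10% against 20% with the ICC: 76% in one sex, 95% combined). Uncommon ones would be seen poorly either way (1% against 3%: 27% and 45%). The documents do not support the stronger claim that stratification will conceal a real harm, nor the claim that a combined analysis has been ruled out.

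**What to change.** In the Outcomes section, keep the sex-specific evaluation and add one sentence: adverse effects are also compared between arms in women and men together, using a mixed model with sex as a covariate and subdistrict as the cluster, and reporting the estimate with its 95% confidence interval. Report the by-sex estimates and their intervals next to the combined one, with equal standing, so that a harm confined to one sex stays visible.

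The cost is one sentence and one extra column or table. No further participants, measurements or staff are needed, and the sex-specific efficacy evaluation is unchanged.

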### Participant timeline, blinding and sample size

Participant timeline is depicted in Fig. 2. The four subdistrict pairs will be included consecutively and undergo identical procedures and time schedules. This design will help to control for seasonal or weather effects. Each pair starts and ends with baseline and follow up surveys in the subdistrict. In the intervention subdistrict, development and implementation of the intervention will take place. The address data will be obtained by the registry office of the city of Bremen. Prospective participants will be recruited via written and telephone contact. A detailed written feedback will be sent to all participants after the follow up survey.

**Fig. 2 Fig2:**
[figure not shown]
Timeline of the OUTDOOR ACTIVE intervention trial

The sample size calculation is based on data gathered during the OUTDOOR ACTIVE pilot study. Accelerometer-based average counts per minute (CPM) will be used for evaluation. Mean CPM ranged from 1587.5 (SD 470.7) to 1697.0 (SD 440.5) in the five highly heterogeneous subdistricts (ICC = 0.0024). CPM were consistently higher in women than in men with only moderate differences for SES. In the OUTDOOR ACTIVE intervention trial, a mean difference of 150 CPM (equivalent to standardized effect size of 0.33) is targeted. Assuming a fixed number of clusters (four intervention, four control), 204 participants will be needed in each study arm (significance level 5% two-sided, power 90%) summing up to 808 for sex-stratified trial evaluation. Assuming a fixed proportion of 30% for dropouts, 144 participants (72 female, 72 male) are needed in each of the subdistricts at baseline.

Since no intervention is developed in the control subdistricts, and active involvement of the study participants is required in the intervention subdistricts, blinding was not a feasible option for the intervention trial. Instead, for communication with the public, the study is separated into two parts: one part containing the surveys (“BUTEN AKTIV Gesundheitsuntersuchung” OUTDOOR ACTIVE health surveys), which take place in all eight subdistricts and focuses on longitudinal aspects of the ageing process; the second part containing the intervention development and implementation, takes only place in the four intervention subdistricts (“BUTEN AKTIV vor Ort” OUTDOOR ACTIVE on-site). Thus, participants of the survey might or might not be aware of the intervention development.

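### The 90% sex-specific power rests on one ICC (0.0024) estimated from five pilot subdistricts, with no allowance for its error and clusters fixed at four per arm

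*Protocol article*

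**What the plan says.** In the Protocol article, under Participant timeline, blinding and sample size, the source of the planning values is plain: "The sample size calculation is based on data gathered during the OUTDOOR ACTIVE pilot study". The variance inputs are "Mean CPM ranged from 1587.5 (SD 470.7) to 1697.0 (SD 440.5) in the five highly heterogeneous subdistricts (ICC = 0.0024"). The target is "a mean difference of 150 CPM (equivalent to standardized effect size of 0.33) is targeted", and the error rates are "significance level 5% two-sided, power 90" per cent. Clusters are held at four per arm. The result is 204 participants per arm, about doubled to a stated total of 808 so that each sex can be evaluated separately. After 30% dropout this becomes 144 per subdistrict at baseline. No interval for the ICC, alternative value or margin is given.

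Under Study setting and participants, "the five subdistricts of the OUTDOOR ACTIVE pilot study are excluded, leaving 53 subdistricts eligible for the study". The same section says "The subdistricts of the city of Bremen are highly heterogeneous". The Background places the pilot thus: "a community-based physical activity program was developed in one urban district in the city of Bremen, Germany".

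**The concern.** An ICC estimated from five clusters has 4 degrees of freedom for its between-cluster part, so it is very imprecise however many people each cluster holds. The article uses the point estimate as if it were exact. It comes from subdistricts that cannot enter the trial, while the trial clusters are drawn from 53 others. With clusters fixed, recruiting more people per subdistrict buys little once the ICC rises, so an optimistic value cannot be repaired later.

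What is at stake is how a null result is read. If men or women show no significant difference, the published 90% invites the conclusion that a 150 CPM effect has been largely ruled out. That is too strong if power was well below 90%.

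**Working it through.** **Inputs.** All are from the sample size section: two-sided 5%, power 90%, difference 150 CPM, d = 0.33 (implied SD 150/0.33 = 454.5), quoted SDs 440.5 and 470.7, ICC ρ = 0.0024, k = 4 clusters per arm. Per sex, 204 per arm gives m = 204/4 = 51 per cluster.

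**1. Reproducing 204.** The individually randomised size is n_I = 2(1.960 + 1.282)²/d². With a fixed number of clusters, n = n_I·k(1 − ρ)/(k − n_I·ρ).
- d = 150/440.5 = 0.3405: n_I = 181.2, rounded up to 182; n = 182 × 4 × 0.9976/(4 − 0.4368) = 203.8, so 204.
- d = 0.33 as stated: n_I = 193.0; n = 193 × 4 × 0.9976/(4 − 0.4632) = 217.8, so 218.

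The stated 204 therefore follows from the smaller quoted SD. Both values of d are carried below.

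**2. Margin.** With design effect DE = 1 + 50ρ, 90% power at 204 per arm needs DE ≤ 204/n_I.
- d = 0.33: 204/192.97 = 1.057, so ρ ≤ 0.057/50 = 0.0011.
- d = 0.3405: 204/181.2 = 1.126, so ρ ≤ 0.126/50 = 0.0025.

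**3. Power per sex at 204 per arm.** Normal: Φ(d/√(2·DE/204) − 1.96). The t version uses a noncentral t with 8 − 2 = 6 df. The last column is the difference detectable with 90% power by the normal formula, 3.242 × √(2·DE/204) × SD, for SD 440.5 / 454.5. For example, at ρ = 0.02: 3.242 × √(4/204) = 0.454, and 0.454 × 440.5 = 200.

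| ICC | DE | Normal, d = 0.33 / 0.3405 | t, 6 df, d = 0.33 / 0.3405 | Detectable CPM (normal) |
|---|---|---|---|---|
| 0.0024 | 1.12 | 88% / 90% | 75% / 77% | 150 / 154 |
| 0.005 | 1.25 | 85% / 87% | 70% / 73% | 158 / 163 |
| 0.01 | 1.50 | 78% / 80% | 62% / 65% | 173 / 179 |
| 0.02 | 2.00 | 65% / 68% | 51% / 53% | 200 / 206 |

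**4. Ceiling.** The formula in step 1 has no solution once ρ ≥ k/n_I: 4/193.0 = 0.021 (d = 0.33) or 4/181.2 = 0.022 (d = 0.3405). Above that, no number of participants in eight subdistricts gives 90%.

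**5. What the pilot can exclude.** The pilot size is not given, so it has to be bounded. Five means spanning 1697.0 − 1587.5 = 109.5 have a variance between 109.5²/8 = 1,499 and 0.3 × 109.5² = 3,597. With equal cluster sizes and the usual analysis-of-variance ICC, that variance equals SD²·F/m_p, where m_p is the number per pilot subdistrict and F = (1 + (m_p − 1) × 0.0024)/0.9976. Taking SD from 440.5 to 470.7, m_p lies between about 62 and 230.

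With R = F/F_{0.025; 4, 5(m_p−1)}, the exact upper limit of the 95% interval is (R − 1)/(R + m_p − 1).
- m_p = 62: 0.12
- m_p = 100: 0.085
- m_p = 200: 0.053
- m_p = 230: 0.05
- m_p infinite: the ratio 0.0024/0.9976 × 4/0.4844 = 0.0199, giving ICC 0.0195

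Conversely, with 100 per pilot subdistrict, an estimate of 0.0024 or less would arise 35% of the time if the true ICC were 0.01, and 20% of the time if it were 0.02.

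**The case against.** Several points on the other side carry weight.

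- **Pairing.** Subdistricts are paired on socioeconomic status and land use, so the variance that matters is what remains within pairs. This stands as a possible gain, but the calculation takes no credit for it. A paired cluster-level analysis would also have only 3 df: with no variance reduction, power at ICC 0.01 would be 46-49%.
- **Baseline measurement.** CPM is measured before and after, and adjusting for baseline could recover much of the loss. The article does not state such adjustment, so this is an assumption. With individual/cluster-level correlations of 0.4/0.6 to 0.6/0.8, power at ICC 0.02 (d = 0.33, normal) would be 78% to 91%.
- **Pooling the sexes.** With m = 102, normal-approximation power is 91-93% at ICC 0.01 and 77-80% at 0.02. This stands, but the article sizes the trial for sex-stratified evaluation.
- **Degrees of freedom.** The drop from 88-90% to 75-77% at ICC 0.0024 is due to the t reference, not the ICC. The table keeps the two effects apart for this reason. The 51-53% at ICC 0.02 combines both.
- **Condensed article.** A sensitivity table may sit in the full protocol. Its absence is not the point; the article states an unqualified 90% that holds only at about one ICC value.

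A reader might go further and infer that the trial is underpowered because the pilot ICC omits between-district and seasonal variance. The documents do not support that. Both members of a pair follow the same schedule, which the article says helps control for season, and no pilot survey dates are given. That all five pilot subdistricts lie in one district is an inference from two sections, and the sample size section calls those subdistricts highly heterogeneous. Nothing shows that the true ICC exceeds 0.0024.

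**Conclusion.** The point holds as a statement about uncertainty. The claimed 90% per sex has no margin above an estimate with 4 degrees of freedom. Over ICC 0.005 to 0.02, power per sex is 87% down to 65% by the article's type of calculation, and 73% down to 51% with 6 cluster-level df. The upper part of that range cannot be dismissed: the 95% upper limit is about 0.05 to 0.12 for pilot sizes compatible with the quoted means, and still about 0.02 for an unlimited pilot, close to the 0.021-0.022 ceiling.

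This rests on 51 participants per sex per cluster, equal pilot cluster sizes, an unadjusted analysis-of-variance ICC, and no gain from pairing or baseline adjustment. The conclusion about imprecision does not depend on the unstated pilot size. The 6 df is also an assumption, since the article names mixed models without a degrees-of-freedom method.

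**What to change.** Replace the unqualified 90% with a short table of sex-specific power, or of the detectable CPM difference, for ICC values from 0.0024 to 0.02. Compute it with a t reference on the cluster-level degrees of freedom, and state which SD is used: 440.5 reproduces 204, while the stated 0.33 does not. If pairing or baseline adjustment is to be credited, give the assumed variance reduction and its source. State in advance that a null sex-specific result will be interpreted against this range, with its confidence interval, and not against a single 90%.

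Re-estimating the ICC from the baseline surveys is optional. Eight subdistricts less four pairs again leave only 4 df, and with clusters fixed the result would change no design decision.

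The cost is one table and a sentence on interpretation. The stated power becomes less favourable; no extra participants or subdistricts are needed.
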